## Data management 

Qualitative interviews and focus group discussions will be recorded on audio recording devices and field notes will be documented on a handheld tablet. Survey responses will also be recorded on a handheld tablet. Audio recording devices and handheld tablets will be stored securely in a locked cabinet or room, accessible only by NEAT researchers, until the data can be uploaded to a computer. Audio recordings, field notes, and survey responses will be uploaded to password protected, encrypted laptops owned by NEAT and shared with the study team using a secure JHU SharePoint account with a built-in encrypted backup solution. Transcription and translation of audio recordings will be completed on NEAT computers and shared with the study team through SharePoint. The original audio recordings will then be destroyed. 

### Limitations

This study may be limited in several ways. For instance, the study sites were selected purposively and are in one of 77 districts in Nepal; therefore, generalizability could be limited. Findings may also be limited to rural settings among certain ethnic groups in Makwanpur and may vary among other geographic or ethnic contexts.

Considering the current COVID-19 pandemic, intervention implementation may be delayed, and data will likely reflect the pandemic’s effects on facility closures, attitudes toward help-seeking, and health-related behaviors. However, both treatment and control facilities will be exposed to the virus and Nepal’s national response, and so no significant differences due to COVID-19 are expected between groups.

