### National Immunization Programme

Since its inception in 1979, Nepal’s National Immunization Programme (NIP) has been one of the government’s highest priorities, aiming to “reduce child mortality, morbidity and disability associated with vaccine preventable disease” (
Ministry of Health Nepal, 2017, n.p.). The program, which originally offered only BCG and Diphtheria Pertussis Tetanus (DPT) vaccines in three districts, expanded in 1988 to cover all 75 districts in the country and also provide oral polio and measles vaccines (
Department of Health Services, 2018). As of 2020, seven vaccines which protect against 11 vaccine-preventable diseases (Diphtheria, Hepatitis B, Hemophilus Influenza B, Japanese Encephalitis, Measles, Pertussis, Polio, Pneumococcal Disease, Rotavirus, Rubella, Tetanus, and Tuberculosis) are offered (
Ministry of Health and Population Nepal, 2020).

Immunization services are primarily delivered through government networks, such as health facilities, outreach clinics, and mobile clinics, but an upward trend of delivery by private institutions is being observed in urban areas (
Child Health Division, 2011). Vaccines and related logistics are provided free of cost to all health facilities, both public and private, by the government (
Child Health Division, 2011;
Department of Health Services, 2018). Many health facilities elect to administer vaccines on one pre-specified day per month, called “Immunization Day.” This system helps providers track vaccine uptake in their communities by reaching all children in need of vaccines on the same day, and it also helps parents remember to bring their child for their next immunization.

The NIP played a major role in meeting the fourth target of the Millennium Development Goals to reduce the number of under-five deaths to less than 40 per 1,000 live births (
Ministry of Health and Population Nepal, 2020;
National Planning Commission, 2017). The country achieved a number of successes, including being declared polio free in 2014, maintaining elimination status of maternal and neonatal tetanus since 2005, controlling rubella and cognitive rubella syndrome in 2018, and progressing towards the elimination of measles (
Department of Health Services, 2018;

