**Figure 1. f1:**
[figure not shown]
Geographical location of study. Note: This figure was adapted from the original image (
NordNordWest, 2019). This image is free to use under the creator’s licensing conditions. Licensing agreement available at
https://creativecommons.org/licenses/by-sa/3.0/de/legalcode.

In each of the three Palikas, we selected one ward (the administrative unit below a Palika) as a treatment site, and chose a clinic in the ward based on our desire to maximize geographic diversity across the three Palikas. Treatment facilities were selected purposively based on relative need for immunization and service delivery support and willingness to collaborate, as the intervention design and implementation would require the input and participation of local stakeholders. We considered other designs (including a cluster randomized study) but decided against it for two reasons. First, it would be hard to justify a random sample when the number of units (in this case Palikas) is only six. Second, we were constrained by resources to expand to more than three intervention Palikas. Given these constraints, it was deemed more useful to choose sites based on specific criteria. For example, for each ward in the treatment arm, we selected another ward and clinic as a control site in that Palika, matched on population characteristics including ethnicity, age distribution, gender ratio, and population size with the treatment ward. Each control facility is located in a separate geographic vicinity from the treatment facility in its Palika to minimize contamination.

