### Study design

We will use a clustered quasi-experimental design with panel data to measure the impact of the intervention on immunization behaviors, intent to vaccinate, and uptake of other health services. Participants from each of the six study sites will complete a baseline survey preceding intervention implementation and an end-line survey approximately eight months later. Data collectors will read questions aloud to participants and then record responses on a handheld tablet. Surveys are available as
*Extended data* (
[name], 2020).

In addition, the physical conditions of the health facilities and immunization centers will be assessed using checklists at baseline. These checklists will be used to corroborate subjective reports from interviews, focus group discussions, and surveys and assist with identifying needed resources to include in the intervention design. Our data collectors will visit each health facility and the surrounding immunization centers on the designated “Immunization Day” to complete the checklists.

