### Quantitative

The primary objective of the quantitative analysis is to determine whether the Rejoice Architecture intervention results in greater vaccination uptake (or intentions for vaccination) among mothers (or prospective mothers) in the treatment, compared to the control, arm. Hierarchical linear regressions (HLM) will be used to test the primary hypothesis that vaccination rates (number of newborns vaccinated divided by total live births within a catchment area) in the treatment group will be significantly greater (goal is 10 percent) than that in the control group. This analysis will take into account the clustered nature of data within each of the six catchment areas (three in treatment and three in control areas).

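### Only the treatment facilities were chosen for need and willingness, so purposive selection threatens the arm comparison itself, in either direction, and not just generalizability

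*Protocol article*

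**What the plan says.** On how sites were chosen, the protocol article (Study setting, text after Figure 1) says: "Treatment facilities were selected purposively based on relative need for immunization and service delivery support and willingness to collaborate". Each treatment ward was then given a control ward in the same Palika, "matched on population characteristics including ethnicity, age distribution, gender ratio, and population size with the treatment ward". Need, willingness, prior coverage and prior trend are not among the named items. The section gives two reasons for not randomizing: the small number of units and limited resources.

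On measurement, Quantitative methods (Study design) has participants at all six sites "complete a baseline survey preceding intervention implementation and an end-line survey approximately eight months later". Contribution to the field adds that baseline data are already in hand and that the intervention will start once travel restrictions are lifted.

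On analysis, Data analysis (Quantitative) states the primary hypothesis that the vaccination rate "in the treatment group will be significantly greater (goal is 10 percent) than that in the control group". The only feature that the model is said to account for is clustering within the six catchment areas.

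On consequences, Limitations says "the study sites were selected purposively and are in one of 77 districts in Nepal; therefore, generalizability could be limited". Its one remark on whether the arms are comparable concerns COVID-19, where no important difference is expected.

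**The concern.** If both arms had been picked by the same purposive rule, the main cost would indeed be generalizability. Here one arm was picked on variables tied to the outcome and the other was not. Need for immunization support is close to selection on the outcome's own level. If need was judged during a temporary dip, part of the later rise is regression to the mean. Willingness to collaborate reflects local leadership, and the article's own background (National Immunization Programme) credits local political ownership for the success of an earlier coverage initiative. Engagement is thus treated as a driver of coverage, is used to choose the treatment sites, and is not named as a matching item.

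The quantitative component is meant to measure impact as rigorously as possible. Followed as written, a ward-specific difference in level or trend would be reported as part of that impact, and a reader of Limitations would not be alerted to it.

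**Working it through.** **The plan's own sample size.** Inputs from Quantitative methods (Sampling): 83% to 93%, alpha 0.05 (taken as two-sided), power 80%, intraclass correlation 0.01, six clusters, 20% attrition.

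- Individually randomized requirement: 165 per arm.
- Design effect at 380/3 = 126.7 per cluster: 1 + (126.7 − 1) × 0.01 = 2.257.
- 165 × 2.257 = 372.4, so 373 per arm, within 3% of the stated 380.
- 380/0.80 = 475 per arm, 950 in total, as stated.

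The sample size reproduces and is not at issue. A larger sample or a cluster adjustment would not remove the bias discussed here.

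**What each contrast would estimate.** Let the starting level be T0 in treatment and C0 in control, the gain without any intervention be gT and gC, and the true effect be E.

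- End-line contrast: E + (T0 − C0) + (gT − gC).
- Change-from-baseline contrast: E + (gT − gC).

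A trend shared by both wards of a pair cancels in both. A fixed level difference cancels only in the second. A differential trend cancels in neither.

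**Direction.** Regression to the mean or engaged leadership makes gT − gC positive and favours treatment. Greater need may mean lower starting coverage, so T0 − C0 is negative and works against treatment in an end-line contrast. For example, assume a starting deficit of 5 points and a differential gain of 2. The end-line contrast gives E − 5 + 2 = E − 3, and the change contrast gives E + 2. The net sign is open.

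**Illustrative size.** The document gives no ward-level trends. The only trend in it is the Sampling section's assumed district rise of about 6 points from 2017 to 2019 without this intervention.

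- Per eight months: 6/2 × 8/12 = 2 points.
- Per 20 months (an assumed interval, if the launch delay stretches it): 6/2 × 20/12 = 5 points.

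If treatment wards rose at twice that pace and controls at that pace (an assumption), the differential gain would be 2 or 5 points. That is 2/10 = 20% or 5/10 = 50% of the goal.

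**Effect on the false-positive rate, same assumptions, E = 0.** Null SE: sqrt(2 × 0.83 × 0.17/380 × 2.257) = 0.041.

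| Assumed bias (points) | Normal test | t test, 4 df |
|---|---|---|
| 0 | 5.0% | 5.0% |
| 2 | 7.8% | 6.7% |
| 4 | 16.4% | 11.9% |
| 5 | 23.1% | 15.8% |

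This SE is that of a single cross-sectional comparison. It equals the SE of a change contrast only if the within-person correlation is 0.5 (an assumption). The rates therefore depend on the test as well as on the assumed bias. The shift in the point estimate does not.

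**The case against.** The case on the other side is substantial, and much of it stands.

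- A reader might infer that Limitations denies the bias. It does not. Its list is introduced as examples, the design is openly called quasi-experimental, and the reasons for not randomizing are given. The section is silent on this threat.
- A reader might infer that controls were matched on four demographic items and nothing else. The list is open-ended, and each control lies in the same Palika, so Palika-wide trends and leadership are shared. Only a ward-specific difference remains, and none is reported.
- A reader might infer that the treatment wards were already improving and that the bias favours the intervention. The document does not show this. Selection for need could equally pull the other way.
- One baseline survey is not wholly uninformative about the past. It enrols mothers of children under 1 year and of children 1–2 years (Table 2), which are two birth cohorts per arm before launch. It allows a coarse check, though not a trend line.
- The district trend compares successive years, whereas change in a panel of the same mothers also reflects children ageing through the schedule. It gives only a scale.
- Model details such as baseline adjustment may sit in an analysis plan that is not shown.

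The core survives. The article itself states an arm-specific selection rule and itself confines the consequence to generalizability. An unseen analysis plan cannot undo the site selection or change the published limitation.

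**Conclusion.** The point holds in a limited form. Selecting treatment facilities, but not controls, on need and willingness can confound the arm comparison through a ward-specific difference in level or trend, in either direction. Limitations names only the effect on generalizability. One survey before launch, with a wait of unknown length between baseline and implementation, gives little means of checking for it, and divergence during the wait would be counted as effect.

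The size is unknown. The figure of 20 to 50% of the 10-point goal rests on an assumed differential gain of 2 to 5 points. The false-positive rates in the table rest on the same assumption and on the choice of test, so they should not be cited as properties of this study. The stronger claim, that an improving ward will be mistaken for impact, goes beyond the document.

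**What to change.** 1. Reword Limitations to say that choosing treatment sites for need and willingness threatens internal validity as well as generalizability, and that the bias could run either way. Temper the causal wording about impact accordingly.

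2. Make the arm contrast one of change from baseline within matched pairs. This removes fixed level differences but not differential trend.

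3. Report each pair's pre-launch coverage as descriptive support. Use the two birth cohorts in the baseline survey, compared at the same ages. Where available, add the lists kept by the Female Community Health Volunteers, which the qualitative Sampling section says record children's immunization status, or facility records. The article says of the monthly Immunization Day that "This system helps providers track vaccine uptake in their communities", which makes such records plausible. It does not show that long monthly series exist, so a time-series analysis should not be made a requirement.

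With three pairs, similarity should be judged by eye. It should not be put to a significance test or used as a pass/fail condition for claiming impact.

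The cost is a wording change and some extra analysis, with no new participants. The downsides are that records may be incomplete (the article cites 52% retention of immunization cards in Nepal) and that the conclusion becomes more cautious.

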### Contribution to the field

Currently in phase 2 of the study, we have collected baseline data and modified the Rejoice Architecture intervention design, and will implement the intervention when COVID-19 travel restrictions are lifted. We expect this project will make incremental, though important contributions to the global efforts in increasing immunization and reducing child mortality. The iterative and multi-phase procedure will allow for constant adaptation of the intervention, driven by a deepened understanding of individual and contextual factors that will be achieved through community-based participation at every phase. This theory-driven approach will offer a novel connection between community-level theory and individual behavior, bridged by changes in social norms. More specifically, this study will test the pathway between physical infrastructure, mothers’ behavior and child immunization, and will therefore provide direction for future research aiming to address immunization uptake and other service use in LMICs.

### Ethics and dissemination

The Institutional Review Boards with Johns Hopkins University (no. 9951) and the Nepal Health Research Council (no. 860/2019) approved this study. All participants will provide written consent before data collection. Findings from this study will be disseminated in participating Palikas and wards in Makwanpur, at international research conferences, and through peer-reviewed journals.

## Data availability

### Underlying data

No underlying data are associated with this article.

### Extended data

Open Science Framework: Rejoice Architecture Meets Social Norms to Accelerate Vaccination in Nepal: Protocol for a Mixed-Method Quasi-Experimental Study.
https://doi.org/10.17605/OSF.IO/JYBK4 (
[name], 2020).

This project contains the following extended data:

Interview and focus group guidesBaseline survey instrumentsConsent forms

Extended data are available under the terms of the
Creative Commons Zero "No rights reserved" data waiver (CC0 1.0 Public domain dedication).
